# 2. INTRODUCTION

## 2.1. Background and rationale

The COVID-19 pandemic is associated with considerable morbidity and mortality. As of May 2021, > 32.6 million COVID-19 cases and > 580,000 attributed deaths have been detected in the USA [[1]](https://www.spiritprotocol.com/api/docx/https://paperpile.com/c/nKRweq/D7DYc). Globally, > 160 million COVID-19 cases and > 3.3 million attributed deaths have been reported [[2]](https://www.spiritprotocol.com/api/docx/https://paperpile.com/c/nKRweq/0puKg). The clinical course of acute COVID-19 is well-described [[3–7]](https://www.spiritprotocol.com/api/docx/https://paperpile.com/c/nKRweq/lU1D+t8iR+K9mW+Mq1f+OJ8y). Post-acute COVID-19 is defined as persistence of symptoms or development of sequelae after 3 or 4 weeks from the onset of acute symptoms of COVID-19 [[8–10]](https://www.spiritprotocol.com/api/docx/https://paperpile.com/c/nKRweq/XHsQi+bmgL6+etRcB). This definition is further divided into subacute or ongoing symptomatic COVID-19, including symptoms from 4-12 weeks beyond acute COVID-19, and a chronic or post-COVID-19 syndrome, which includes symptoms persisting or present beyond 12 weeks of acute COVID-19 not attributable to alternative diagnoses [[8,11]](https://www.spiritprotocol.com/api/docx/https://paperpile.com/c/nKRweq/XHsQi+1Igm8). Information on post-acute COVID-19 and long-term sequelae of SARS-CoV-2 infection is only recently emerging [[12–15]](https://www.spiritprotocol.com/api/docx/https://paperpile.com/c/nKRweq/DBuqU+NqrkR+3wwBG+PRH0f).

To characterize post-COVID-19 syndromes better, there is an urgent need for broader representation in study population selection to allow for representativeness and generalizability, to set objective outcomes that are not limited to symptoms but include illness events and clinical events, and to include SARS-CoV-2 negative individuals to ensure other effects of the pandemic are considered in the analysis (e.g. impact on livelihoods, mental health, food security, and mobility) [[16]](https://www.spiritprotocol.com/api/docx/https://paperpile.com/c/nKRweq/38UeS). Such work will help clinicians know what post-infectious sequelae to expect and who is at increased risk, will help ensure research findings can be compared across studies, and will move us towards addressing critical health care response needs.

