## 3.2. Eligibility criteria

This study includes adult patients who are under clinical investigation for possible SARS-CoV-2 infection and who meet inclusion criteria outlined in Table 1. We include individuals with symptomatic presentation to determine comparative frequency of outcomes amongst symptomatic individuals with and without SARS-CoV-2 infection: symptomatic individuals presenting with covid-like illness who test negative will act as controls for symptomatic individuals who have positive tests for SARS-CoV-2. Asymptomatic individuals are not eligible, given the anticipated lower rates of outcomes among asymptomatic individuals who test positive for SARS-CoV-2, and the significant heterogeneity in reasons for testing in asymptomatic individuals, such as screening for social, educational, occupational reasons and prior to routine clinical procedures. Individuals who self-report symptoms suggestive of acute SARS-CoV-2 infection, and are tested for SARS-CoV-2 within the last 42 days, are eligible to participate. From study initiation through the summer of 2021, symptoms of acute SARS-CoV-2 was defined using the COVID-19 clinical criteria case definition (Table 2) [[18]](https://paperpile.com/c/nKRweq/MqHQg); beginning summer of 2021, in order to capture less symptomatic individuals, the inclusion criteria were revised to require only one symptom among those listed in Table 2. Individuals for whom a SARS-CoV-2 test result cannot be confirmed are not eligible to participate in the study. Efforts are made to recruit participants from across the spectrum of COVID-19 illness severity, including individuals from outpatient (e.g., drive through testing with self-reported symptoms) to inpatient settings, and those cared for in intensive care units. We seek to enroll using a 3:1 case/control ratio to oversample those who are positive for SARS-CoV-2 on testing, while still ensuring an adequate control cohort for comparison.

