**Table 1: Inclusion and exclusion criteria**

Inclusion criteria:

1. Fluent in English or Spanish
2. Age 18 years or older
3. Self-reported symptom suggestive of acute SARS-CoV-2 infection [[19]](https://www.spiritprotocol.com/api/docx/https://paperpile.com/c/nKRweq/KvIKQ)
4. Tested for SARS-CoV-2 with any FDA-approved or authorized viral test (i.e., nucleic acid amplification test or antigen test [[20]](https://www.spiritprotocol.com/api/docx/https://paperpile.com/c/nKRweq/mGkhJ)) within 42 days of enrollment

Exclusion criteria:

1. Unable to provide informed consent
2. Study team unable to confirm the result of a diagnostic test for SARS-CoV-2
3. Does not have access to a hand-held device or computer that would allow for digital participation in the study
4. Lawfully imprisoned while participating in the study

**Table 2: COVID-19 clinical criteria case definition (August 2020)** [[18]](https://www.spiritprotocol.com/api/docx/https://paperpile.com/c/nKRweq/MqHQg)

*In the absence of a more likely diagnosis,*

At least TWO of the following symptoms:

- Fever (measured or subjective)
- Chills
- Rigors
- Myalgia
- Headache
- Sore throat
- Nausea or vomiting
- Diarrhea
- Fatigue
- Congestion or runny nose

Or any ONE of the following symptoms:

- Cough
- Shortness of breath
- Difficulty breathing
- New olfactory disorder
- New taste disorder

Or severe respiratory illness with at least ONE of the following:

- Clinical or radiographic evidence of pneumonia
- Acute respiratory distress syndrome (ARDS)

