## 3.3. Recruitment

Participant Identification and Enrollment

Methods used to recruit potentially eligible participants vary by site, although each site applies the same eligibility criteria described in Table 1. Most sites screen for eligible participants among those tested for SARS-CoV-2 infection. With this process in place, we seek to enroll participants as close to their initial date of SARS-CoV-2 testing as possible. Identification and enrollment methods include: i) a member of the study team accesses the EMR to screen for potentially eligible individuals based on SARS-CoV-2 testing and reason for testing and contact eligible individuals, ii) participants learn of the study from a poster, brochure, or social media and can enroll directly through the online portal, iii) research staff reach out to potentially eligible individuals in-person, over the phone, or by text or e-mail to offer and facilitate enrollment (e.g., contact information obtained from organizations including city and state agencies conducting SARS-CoV-2 testing). The method or combinations of methods used at each site are based on local IRB approval and practical considerations. Though minor differences exist across sites, the study eligibility criteria, online enrollment, and data collection methods are identical, which allows for compilation and comparison of data across sites.

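### The 42-day enrolment window outlasts the protocol's 3-to-4-week start of post-acute COVID-19, so late self-enrolment may select on persisting symptoms and a comparison restricted to early enrollees is needed

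*Protocol*

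**What the plan says.** Protocol Table 1 requires a viral test "within 42 days of enrollment", and section 3.2 repeats the rule: people who "are tested for SARS-CoV-2 within the last 42 days, are eligible to participate". The symptom criterion is "Self-reported symptom suggestive of acute SARS-CoV-2 infection"; it carries no onset date and no limit on the time from onset to test.

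Section 2.1 describes post-acute COVID-19 as "persistence of symptoms or development of sequelae after 3 or 4 weeks from the onset of acute symptoms of COVID-19". It then separates a subacute phase ("symptoms from 4-12 weeks beyond acute COVID-19") from a chronic one ("symptoms persisting or present beyond 12 weeks of acute COVID-19").

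On recruitment, section 3.3 states an aim: "we seek to enroll participants as close to their initial date of SARS-CoV-2 testing as possible". It says most sites screen among people who were tested. It also lists an open route, in which "participants learn of the study from a poster, brochure, or social media and can enroll directly through the online portal". Section 3.1 adds that enrolment can be completed without research staff.

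Section 3.9.1 compares positives with negatives and names age, sex, race/ethnicity, income and underlying conditions among its adjustment factors. The sensitivity analyses it names concern missing data only.

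**The concern.** The objective is sequelae, and participants know their test result when they decide whether to join. A test-positive person still unwell in week 5 has an obvious reason to join a registry about the after-effects of COVID-19. A recovered positive, or a test-negative person, has less reason. Entry can then depend jointly on exposure and on persisting symptoms. That is selection bias, and adjusting for demographics and comorbidity does not address it. Nothing in the eligibility criteria prevents it, and the aim of early enrolment sets no limit.

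At stake is the central contrast of the study. A large sample gives no protection, because it makes a spurious difference more likely to reach significance.

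**Working it through.** **1. Overlap of the window with the post-acute period.** Inputs: 42 days (Table 1); 3 or 4 weeks, i.e. 21 or 28 days (section 2.1).

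- Past 3 weeks: 42 − 21 = 21 days, 21/42 = 50% of the window.
- Past 4 weeks: 42 − 28 = 14 days, 14/42 = 33%.

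The clocks differ: the window runs from the test, the definition from symptom onset. Onset before the test widens the overlap. With an assumed 5-day delay from onset to test, a day-42 entrant is 42 + 5 = 47 days from onset. Onset after the test narrows it.

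**2. The plan's own power figure.** Section 3.8 assumes 3,600 positives, 1,200 negatives, a 2.5% control rate and alpha 0.05, and states 97.8% power for a 2.5-point difference. Two-sided, with pooled variance under the null:

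- pooled rate = (3,600 × 0.05 + 1,200 × 0.025)/4,800 = 0.04375
- SE0 = √[0.04375 × 0.95625 × (1/3,600 + 1/1,200)] = 0.00682
- SE1 = √[0.05 × 0.95/3,600 + 0.025 × 0.975/1,200] = 0.00579
- power = Φ[(0.025 − 1.96 × 0.00682)/0.00579] = Φ(2.01) = 97.8%

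The figure reproduces. It does not speak to selection.

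**3. Possible size of the bias.** The documents do not give the share enrolled late or through the open route, so the following values are assumed. True risk is r = 2.5% in both groups. A share f of positives comes in late, and within that share affected people are k times as likely to join. Negatives have no such selection. With m = fk + (1 − f), the apparent risk in positives is rm/(rm + 1 − r).

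| f | k | m | Apparent risk | Risk ratio | Chance of a significant excess in positives |
|---|---|---|---|---|---|
| 10% | 1.5 | 1.05 | 2.6% | 1.05 | 4% |
| 25% | 2 | 1.25 | 3.1% | 1.24 | 17% |
| 50% | 2 | 1.50 | 3.7% | 1.48 | 51% |
| 50% | 3 | 2.00 | 4.9% | 1.95 | 97% |

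The first row is negligible. The last is about as large as the 2.5-point difference the study is powered to detect.

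**4. Would days from test to enrolment, used as a covariate, remove it?** Take f = 50%, k = 2. Early stratum: 2.5% against 2.5%, ratio 1.0. Late stratum: 2 × 0.025/(2 × 0.025 + 0.975) = 4.88% against 2.5%, ratio 1.95. With the same late share in both groups, the ratio standardised over strata is (0.5 × 2.5 + 0.5 × 4.88)/2.5 = 1.48, the same as the crude ratio. Adjustment removes nothing, because the selection acts within the late stratum. Separating the strata does reveal it.

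**5. Precision of a restricted comparison.** Repeat step 2 with fewer people; the excluded shares are assumed.

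- One third of each group excluded (2,400 and 800): SE0 = 0.00835, SE1 = 0.00709, power = Φ(1.22) = 89%.
- Half of each group excluded (1,800 and 600): SE0 = 0.00964, SE1 = 0.00819, power = Φ(0.75) = 77%.

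**The case against.** A reader might infer that late entrants already have the study's outcome. The documents do not support that in general. ME/CFS requires impairment lasting more than 6 months (Table 3), and section 2.1 places the chronic syndrome beyond 12 weeks. Follow-up assessments start 3 months after enrolment (section 3.14), so a day-42 entrant is first surveyed roughly 4.5 months after the test. For these outcomes the risk is enrichment. The stronger label fits only early symptom persistence and duration.

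Entry does not require current symptoms, and the same window applies to test-negative controls. This stands: the contrast is biased only if persistence drives enrolment more strongly in positives. That is plausible, but the documents do not show it.

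The larger ratios rest on many people entering late and on treating week-5 symptoms and the later outcome as the same thing. This also stands. Take a 5% outcome, one third late and two-fold selection. Late positives show 0.10/(0.10 + 0.95) = 9.5%, all positives 2/3 × 5% + 1/3 × 9.5% = 6.5%, ratio 1.30. Now suppose 30% are symptomatic at week 5, including all of that 5% (assumed). Late positives show 0.10/1.30 = 7.7%, all positives 5.9%, ratio 1.18. Section 3.3 points to a modest late share: two of its three routes are staff-initiated and early enrolment is sought.

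Finally, sensitivity sets and covariates commonly sit in the SAP, which was not available here, and the covariate list in 3.9.1 is open-ended. It would be wrong to say the plan excludes such an analysis. But the window and the open route are fixed by the protocol itself, and none of the sensitivity analyses it does name addresses their consequence.

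**Conclusion.** The point holds as a foreseeable selection risk created by the protocol's own window and recruitment route. It is not a demonstrated bias. One third to one half of the window lies past the post-acute threshold of section 2.1, subject to the difference between test and onset clocks. The distortion could be trivial or decisive: a risk ratio of about 1.05 to 1.95 under the assumed late shares and selection strengths. The documents do not allow a narrower statement.

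Two further inferences should be resisted. Days from test to enrolment, entered as a covariate, would not remove the bias (step 4). And 28 days from the test is not the protocol's own limit: section 2.1 says 3 or 4 weeks and counts from onset, so someone tested a week after onset and enrolled on day 27 is already 34 days from onset.

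**What to change.** Leave the 42-day window and the full-cohort main analysis as they are. In section 3.9.1, or in the SAP if it does not already do so:

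- Pre-specify the positive-versus-negative comparison of symptom and sequelae outcomes among participants enrolled within 28 days of the index test, and again within 21 days, since section 2.1 gives both thresholds.
- Report early and late enrollees side by side, and qualify the conclusion if they differ.
- Do not rely on days to enrolment as an adjustment covariate for this purpose.
- Show results by recruitment route only if route is recorded per participant. The protocol does not say that it is, and capturing it would be a new data item.

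The restricted comparisons need only the test and enrolment dates, which the 42-day rule already requires, so no extra patients or procedures are involved. The cost is precision: for 5.0% against 2.5%, about 89% power if one third of each group is excluded and about 77% if half is, instead of 97.8%. Restriction reduces the bias but does not guarantee its removal, since some selection may act before day 21 or 28 and onset may precede the test.

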## 3.3. Recruitment

Participant Identification and Enrollment

Methods used to recruit potentially eligible participants vary by site, although each site applies the same eligibility criteria described in Table 1. Most sites screen for eligible participants among those tested for SARS-CoV-2 infection. With this process in place, we seek to enroll participants as close to their initial date of SARS-CoV-2 testing as possible. Identification and enrollment methods include: i) a member of the study team accesses the EMR to screen for potentially eligible individuals based on SARS-CoV-2 testing and reason for testing and contact eligible individuals, ii) participants learn of the study from a poster, brochure, or social media and can enroll directly through the online portal, iii) research staff reach out to potentially eligible individuals in-person, over the phone, or by text or e-mail to offer and facilitate enrollment (e.g., contact information obtained from organizations including city and state agencies conducting SARS-CoV-2 testing). The method or combinations of methods used at each site are based on local IRB approval and practical considerations. Though minor differences exist across sites, the study eligibility criteria, online enrollment, and data collection methods are identical, which allows for compilation and comparison of data across sites.

## 3.4. Interventions

### 3.4.1. Intervention description

This is a prospective, observational study without an intervention.

## 3.5. Outcomes

Patient reported outcomes include self-reported disease-specific and generic health measures (Appendix A) [[21–23]](https://www.spiritprotocol.com/api/docx/https://paperpile.com/c/nKRweq/VLC3Q+9tpIp+1b0NF). Health care utilization and clinical events are extracted from the EMR data via Hugo as well as collected via patient self-report, ensuring uniform variable definitions across participating sites.

Self-report of symptoms suggestive of SARS-CoV-2 are assessed using questions derived from the Centers for Disease Control and Prevention (CDC) Person Under Investigation for SARS-CoV-2 survey (Appendix A) [[24]](https://www.spiritprotocol.com/api/docx/https://paperpile.com/c/nKRweq/QL4WH). This is not scored and has no predefined cutoff for the likelihood of COVID-19 illness.

Generic physical and mental health is assessed using the PROMIS^®^-29 [[25]](https://www.spiritprotocol.com/api/docx/https://paperpile.com/c/nKRweq/sSZ6k). This measure assesses pain intensity using a single 0-10 numeric rating item, and seven health domains (physical function, fatigue, pain interference, depressive symptoms, anxiety, ability to participate in social roles and activities, and sleep disturbance) using five response options per domain ranging from “not at all” to “very much”. In prior studies, this measure exhibits high reliability and validity, correlating well with other physical and mental health surveys as well as with chronic disease. The PROMIS^®^ instrument assesses health-related quality of life over the past seven days, except for two domains (physical function and ability to participate in social roles and activities) which do not specify a timeframe. Raw PROMIS^®^-29 scores are re-scaled from raw scores of 8 (worst) to 40 (best) into standardized T-score with a mean of 50 and standard deviation (SD) of 10. A higher PROMIS^®^ T-score represents more of the concept being measured. For negatively worded concepts like Anxiety, a higher score is worse. For positively worded concepts like Physical Function-Mobility, a higher score is better. Version 2.1 of the PROMIS^®^-29, which will be used in the present study, is rescaled into a generic, societal, preference-based summary score [[26]](https://www.spiritprotocol.com/api/docx/https://paperpile.com/c/nKRweq/smMJA). This is based on PROMIS^®^ scores for Cognitive Function, Abilities, Depression, Fatigue, Pain Interference, Physical Function, Sleep Disturbance, and Ability to Participate in Social Roles and Activities. It is scaled from 0 (equal to death) to 1 (equal to perfect health). Version 2.0 PROMIS^®^ scores can also be used to estimate a Health Utility Index Mark 3 preference score [[27]](https://www.spiritprotocol.com/api/docx/https://paperpile.com/c/nKRweq/0S9Lw). In other settings, differences of 0.03 to 0.1 in this preference score have been interpreted as being clinically important [[28–30]](https://www.spiritprotocol.com/api/docx/https://paperpile.com/c/nKRweq/Iu5iR+gmyam+fWtpT). A cutoff of 0.7 is used to determine severe impairment [[31]](https://www.spiritprotocol.com/api/docx/https://paperpile.com/c/nKRweq/wG4sA).

Cognition is assessed using the survey questions from the Patient-Reported Outcomes Measurement Information System (PROMIS^®^) Cognitive SF 8 [[32]](https://www.spiritprotocol.com/api/docx/https://paperpile.com/c/nKRweq/MUfAZ). Raw PROMIS^®^ Cognitive scores are re-scaled from raw scores of 8 (worst) to 40 (best) into standardized T-scores with a mean of 50 and standard deviation (SD) of 10. A higher score is interpreted as indicating greater cognition.

Health care process measures are assessed as ambulatory care and/or emergency department (ED) visits for symptoms related to COVID-19 illness as well as hospitalization (admitted to hospital overnight during study follow-up) as determined by data from the EMR.

Hospital-free and intensive care unit (ICU)-free survival are assessed as determined by data from the EMR [[33]](https://www.spiritprotocol.com/api/docx/https://paperpile.com/c/nKRweq/7mLIq). Hospital-free survival is survival without any hospitalizations and ICU-free survival is survival without time spent in the ICU.

Additional outcomes  assessed include post-infectious sequelae (e.g., dyspnea, cough) [[34–36]](https://www.spiritprotocol.com/api/docx/https://paperpile.com/c/nKRweq/crjeV+MWglS+v2y9g), post-traumatic stress disorder (PC-PTSD-5) [[37]](https://www.spiritprotocol.com/api/docx/https://paperpile.com/c/nKRweq/dFlhd), and exercise (exercise vital sign; 2 question survey to assess habitual physical activity) [[38–40]](https://www.spiritprotocol.com/api/docx/https://paperpile.com/c/nKRweq/E8xYP+3XcZq+NP9GE), using previously validated questionnaires .

Social determinants of health (e.g., housing, available social services, geographical location, and education) are assessed using a previously validated questionnaire [[41]](https://www.spiritprotocol.com/api/docx/https://paperpile.com/c/nKRweq/tBxfV).

Work and activity status are assessed using questions about returning to work, missed work and activity level (Appendix A).

Myalgic encephalomyelitis/chronic fatigue syndrome (ME/CFS) is assessed using the CDC Short Symptom Screener (Appendix A), following 2015 Institute of Medicine diagnostic criteria (Table 3) [[42]](https://www.spiritprotocol.com/api/docx/https://paperpile.com/c/nKRweq/JxTww). While the study design will allow for assessment of a range of clinical outcomes as well as correlation with various clinical syndromes, recognizing that early reports of post-COVID sequelae may overlap with ME/CFS, this syndrome is included as one of the specific outcomes assessed.

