## 3.9. Statistical methods

### 3.9.1. Outcomes

Statistical analyses will describe disease course and outcomes, including the characterization of specific symptoms and duration of symptoms, health care utilization (emergency department, hospitalization, post-acute care) with clinical (morbidity/mortality) and patient-reported health status outcomes as well as recovery (early and late disease sequelae). Baseline and demographic characteristics will be summarized by descriptive summaries (e.g., means and standard deviations for continuous variables such as age and percentages for categorical variables such as gender, medians, and quartiles for skewed data). Analyses will:

- Compare health status at baseline and follow-up between persons in the same age group who test SARS-CoV-2 positive and negative at initial test.
- Characterize health care utilization (ambulatory and ED visits, hospitalizations, post-acute care, telehealth visits) among SARS-CoV-2 positive participants by age and compare these to SARS-CoV-2 negative participants.
- Characterize and compare health outcomes by age and SARS-CoV-2 status: emergency or ambulatory care, admission to hospital); ICU-free survival;^16^ hospital-free survival; and subsequent patient-reported health status (cognition; physical health; mental health; and return to work).

We will use statistical modeling to estimate the association between key covariates and outcomes, including evaluating interactions by age. We plan to use survival analysis techniques to analyze time to outcome events, logistic regression for binary outcomes (e.g., hospitalization versus no hospitalization), Poisson or Cox regression for count data (e.g., number of hospitalizations over time), and linear regression models for continuous outcomes (e.g., PROMIS-29). Multiple imputation will be considered to handle missing covariate and outcome data in these analyses [[43]](https://www.spiritprotocol.com/api/docx/https://paperpile.com/c/nKRweq/3dpny). Chained equations will be used to impute each variable with missing data. Sensitivity analyses will be conducted using missing categories for covariates and including only people with non-missing outcome information.

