## 3.14. Participant timeline

Figure 1. Participant Timeline

|  | Enrolment | Post-enrollment |  |  |  |  |  | Close-out |
| --- | --- | --- | --- | --- | --- | --- | --- | --- |
| TIMEPOINT | 0 | 3 mos. | 6 mos. | 9 mos. | 12 mos. | 15 mos. | 18 mos. | tx |
| ENROLLMENT: |  |  |  |  |  |  |  |  |
| Eligibility screen | X |  |  |  |  |  |  |  |
| Informed consent | X |  |  |  |  |  |  |  |
| ASSESSMENTS: |  |  |  |  |  |  |  |  |
| Age, gender, symptoms of SARS-COV-2 infection, recent health care use, social determinants of health | X |  |  |  |  |  |  |  |
| Outpatient visit, emergency department visit, hospitalization, intensive care stay, death, physical and mental health (PROMIS-29), cognitive SF-8, hospital-free survival, intensive care-free survival, dyspnea, cough, exercise, social determinants of health, work and activity status, myalgic encephalomyelitis/chronic fatigue syndrome |  | X | X | X | X | X | X | X |
| Preexisting conditions |  | X | X | X | X |  |  | X |

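### Protocol Section 3.5 ties ambulatory and ED visits to COVID-19 with no rule independent of the test result, while Sections 3.9.1 and 3.14 list the same visits unrestricted

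*Protocol*

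**What the plan says.** Section 3.5 is the only place where the protocol defines the visit outcome. It counts "ambulatory care and/or emergency department (ED) visits for symptoms related to COVID-19 illness". The same sentence goes on to "hospitalization (admitted to hospital overnight during study follow-up) as determined by data from the EMR", so admissions carry no restriction by cause.

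Section 3.9.1 sets out the analysis: "Characterize health care utilization (ambulatory and ED visits, hospitalizations, post-acute care, telehealth visits) among SARS-CoV-2 positive participants by age", and then "compare these to SARS-CoV-2 negative participants". Its next bullet again names emergency and ambulatory care among the outcomes compared by SARS-CoV-2 status. Neither bullet limits the visits to COVID-19.

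The participant timeline in Section 3.14 (Figure 1) lists "Outpatient visit, emergency department visit, hospitalization, intensive care stay, death", also without a limit by cause.

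The comparison group is fixed in Section 3.2: "symptomatic individuals presenting with covid-like illness who test negative will act as controls for symptomatic individuals who have positive tests for SARS-CoV-2". Section 2.1 explains why such people are needed: "to include SARS-CoV-2 negative individuals to ensure other effects of the pandemic are considered in the analysis".

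**The concern.** There are two linked problems.

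First, the protocol gives two different outcomes for one comparison. An analyst following Section 3.5 would count only visits tied to COVID-19. An analyst following Section 3.9.1 or Figure 1 would count every ambulatory or ED visit.

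Second, the Section 3.5 version is a poor choice for comparing people with and without the infection. Whether a visit for cough or fatigue is taken to be related to COVID-19 may depend on whether the person tested positive. Under Section 3.6.1, study staff confirm the result from the medical record or from an image sent by the participant, so the participant, and often the treating clinician, can be expected to know it. Section 3.16 provides no masking. If positives' visits are more readily attributed to COVID-19 than negatives' visits for the same complaint, part of the difference in utilization would reflect labelling rather than need for care. A larger sample would not remove that.

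**Working it through.** **Step 1. Set the sections side by side.**

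| Place | Ambulatory / ED visits | Hospitalization |
|---|---|---|
| Section 3.5 (definition) | limited to COVID-19-related symptoms | any overnight admission |
| Section 3.9.1 (comparison by test status) | no limit | no limit |
| Section 3.14, Figure 1 (schedule) | no limit | no limit |

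The restriction appears once, in the only definition, and is absent from the analysis and the schedule. No section says which governs.

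**Step 2. Choose a test and check it against the protocol's own power figure.** The protocol states no figure for visits. Section 3.8 does give 97.8% power for a 2.5-point difference with 3,600 positives and 1,200 negatives, a 2.5% baseline rate and alpha 0.05. Using a two-sided two-proportion test with pooled variance under the null:

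power = Φ[(|p₁ − p₀| − 1.96·SE₀) / SE₁]

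Here SE₀ = √[p̄(1 − p̄)(1/3600 + 1/1200)] and SE₁ = √[p₁(1 − p₁)/3600 + p₀(1 − p₀)/1200].

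With p₁ = 0.05, p₀ = 0.025 and p̄ = 0.04375, SE₀ = 0.00682 and SE₁ = 0.00579, so power = Φ(2.01) = 0.978. This agrees with the protocol, so the same test is used below.

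**Step 3. Illustrate the effect of differential attribution.** The visit rate v and the attribution probabilities a₊ (positives) and a₋ (negatives) are assumptions; the protocol gives none of them. With the same true visit rate v in both groups:

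observed rate = v × a, and observed risk ratio (RR) = a₊ / a₋

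The spurious risk ratio does not depend on v. The chance of a nominally significant result does.

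| v (both groups) | a₊ | a₋ | Observed, positive vs negative | RR | Chance of p < 0.05 with no true difference |
|---|---|---|---|---|---|
| 10% | 0.90 | 0.90 | 9.0% vs 9.0% | 1.00 | 5% |
| 10% | 0.90 | 0.70 | 9.0% vs 7.0% | 1.29 | 58% |
| 10% | 0.90 | 0.50 | 9.0% vs 5.0% | 1.80 | 99.8% |
| 10% | 0.90 | 0.30 | 9.0% vs 3.0% | 3.00 | about 100% |
| 5% | 0.90 | 0.70 | 4.5% vs 3.5% | 1.29 | 31% |
| 5% | 0.90 | 0.50 | 4.5% vs 2.5% | 1.80 | 90% |

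Second row in full: p̄ = (3600 × 0.09 + 1200 × 0.07)/4800 = 0.085, SE₀ = 0.00930 and SE₁ = 0.00877. The chance is Φ[(0.02 − 1.96 × 0.00930)/0.00877] = Φ(0.20) = 0.58.

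**Step 4. Find which outcomes are exposed.** Only ambulatory and ED visits carry the restriction. Hospitalization, hospital-free and ICU-free survival, the PROMIS measures and ME/CFS do not.

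**The case against.** The strongest reply is that the Section 3.5 phrase can be read as a type of symptom rather than an attribution to the disease. Both groups enter with a similar illness, Table 2 lists the symptoms, and both answer the same symptom questions. On that reading a test-negative person's visit for cough counts exactly as a test-positive person's does, and no dependence on exposure is built in. This reading is available. Its support is limited: Section 3.2 has a separate term for COVID-like illness, Section 3.5 elsewhere uses COVID-19 illness for the disease itself, and the definition does not point to Table 2. It does show that the bias is conditional.

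It can also be said that Section 3.9.1 already describes an unrestricted comparison. If that section governs, no labelling problem arises. This is a fair possibility, but the protocol does not say so, and the conflict remains.

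A third reply is that code lists and visit classification usually belong in a statistical analysis plan, and survey content in an appendix, neither of which is shown. That is accepted. The absence of a code list is not the point; the point is a definition that conflicts with the protocol's own analysis section and is unsuited to the comparison.

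A reader might go further and infer that the outcome definition contains the exposure, so that the difference is certainly inflated, perhaps several-fold. For example, a 20% visit rate with 60% versus 10–30% attribution gives 12% versus 2–6%, a risk ratio of 2 to 6. The arithmetic is right, but every input is assumed, and equal attribution gives 1.0.

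**Conclusion.** The point holds as an inconsistency with a conditional risk of bias. Section 3.5 restricts ambulatory and ED visits in a way that Sections 3.9.1 and 3.14 do not, and the visits are compared across test status. If the restricted definition is applied and attribution depends on the known result, the comparison could be biased, most likely away from the null. Under assumed attribution of 90% in positives and 70% to 30% in negatives, the spurious risk ratio runs from 1.29 to 3.0; with equal attribution there is none. The protocol supplies no attribution rates, so neither the presence nor the size of bias can be established from it.

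A reader might also infer that the purpose of the test-negative controls is defeated. The document does not support that: the restriction touches one utilization outcome and leaves the others listed in step 4 of the working untouched, and the primary outcome in the trial summary is sequelae, not visits. The correction is worth making, but it is not essential to the validity of the study as a whole. Confidence is moderate, because the symptom-type reading cannot be excluded.

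**What to change.** Reconcile Sections 3.5, 3.9.1 and 3.14 on one definition. For the comparison by test status, define the outcome as all-cause ambulatory visits and all-cause ED visits, counted identically in both groups.

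If a symptom-specific version is wanted, add it as a secondary outcome. Base it on one prespecified list of symptoms or diagnoses, applied in the same way to both groups and without regard to test result. Table 2 alone would not serve: it is an acute case definition, conditional on there being no likelier diagnosis, and it omits cognitive problems, which the study measures later. The list should cover post-acute symptoms as well. Visits attributed to COVID-19 can still be reported, but only descriptively.

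The cost is a wording change in three places and, for the optional secondary outcome, the preparation of a list. Portal data on visits already flow through the Hugo platform (Section 3.6.1), so no new data collection is needed. The drawback is that all-cause visits include some unrelated to the illness, which dilutes the contrast between groups.
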